### Exclusion criteria

2.5

Patients who present hypotension before photobiomodulation; pregnant women; glaucoma patients; carriers of electronic implants, such as cardiac pacemakers; epilepsy; seizures; history of neoplasias; and patients with photosensitivity.

### Group composition and randomization: (recruitment and randomization)

2.6

Recruitment will be carried out respecting Resolution 466/2012, which regulates human research in Brazil. The patients recruited will have their multiprofessional charts analyzed for demographic and descriptive characterization of the sample.

Nursing consultations in the form of a home visit, or not—at the discretion of the participant, will be scheduled to give healthcare guidance, for an initial interview, completion of the clinical file, and realization of hemodynamic and anthropometric measurements, as well as blood collection and photobiomodulation interventions.

For the application of the photobiomodulation, the participant will place a bracelet where the tip of the coupled laser equipment will be positioned on the radial artery.

We will use the randomization mechanism provided by Sealed Envelope Ltd. (London, UK)^[22]^ Participants will be randomized into blocks of 8 individuals, comprising 4 study groups. They will be identified by sequential numbers, according to the order of recruitment. Immediately before starting treatment, the researcher will look at the randomized list and, using their identification number, verify which group the participant belongs to. The patient will not know to which group he or she has been allocated; only the researcher who will do the irradiations will know. The analysis of the data will be performed by a third person who will also not know group allocations.

A schematic diagram of time schedule of enrolment and interventions of the research groups is summarized in Figure 1.

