### Sample size

2.3

The determination of the number of patients necessary was calculated using G ∗ Power software (version 3.1.9.2, Franz Faul, Universität Kiel, Germany), in which the values for the mean and standard deviation of the primary outcome variable (systolic or diastolic BP) came from the article by Pereira et al.^[21]^ The calculation was performed using the ANOVA repeated measures, with a significance of 5% and power of test at 95%. According to sample calculation, 44 hypertensive patients will be divided into 4 groups with 11 individuals each.

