During the study, strategies will be follow to improve adherence to intervention protocols, as nursing consultations in the form of a home visit, or not—at the discretion of the participant. In addition, patients who have a prescription for drug therapy should not suspend it. All patients, regardless of pharmacological or nonpharmacological use, will receive guidelines for the nonpharmacological treatment of hypertension, focusing on the need to maintain a healthy lifestyle, minimizing risk factors for hypertensive disease. These orientations include directions for healthy eating with decreased levels of sodium, fat, and sugar; regular physical exercise with the supervision of a professional; the need for quality sleep of at least 6 to 8 hours; abandonment or diminution of smoking; and the need for stress-minimizing leisure. Patients taking medication will have guidelines regarding the adequate use of medications, respecting the dose and prescribed schedule, reinforced.

Patients have autonomy for discontinue interventions and in this case, they will be replaced, but the same allocation will be remaining. Any outcome data collected from patients will be disconsidered and the participants will remain in ambulatory care.

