### Procedure for data collection, blinding, and photobiomodulation

2.8

A researcher will generate the allocation sequence using the Sealed Envelope Ltd. An examiner will enroll and assign participants to interventions, performing anthropometric assessments, measurement of hemodynamic variables, and blood collection. Other one will be trained to perform the photobiomodulation and will process the blood samples. Other researcher will perform the statistical analyzes of the results without having participated in the collection of data or the application of the procedures. In this way, the last researcher and the patients will be blind. Only after the end of the trial, the participants will know the allocation and results.

A data collection instrument was developed to contain the information needed to achieve the proposed objectives. The variables will be addressed in categories: characterization of the sample, evaluation of risk factors for cardiovascular disease, anthropometric data, data referring to BP measurements, heart rate, biochemical markers before and after photobiomodulation, as well as approach to the use of medicines, diet, and complementary information.

The photobiomodulation will be applied using the Therapy XT laser equipment, brand DMC, Brazil, following the parameters described in Table 1.

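### Blocks of 8 do not guarantee the stated 11 per group, because 44 is not a multiple of 8

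*Protocol article*

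**What the plan says.** Section 2.6 (Group composition and randomization) gives one block size and no other: "Participants will be randomized into blocks of 8 individuals, comprising 4 study groups". Section 2.3 (Sample size) fixes the total and the split: "44 hypertensive patients will be divided into 4 groups with 11 individuals each". The group descriptions under Figure 1 repeat N = 11 for Laser 60, Placebo 60, Laser 30 and Placebo 30.

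On patients who discontinue, the text after those descriptions says "they will be replaced, but the same allocation will be remaining". A replacement therefore takes over the place of the patient who left.

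On access to the list, section 2.6 says that just before treatment "the researcher will look at the randomized list and, using their identification number, verify which group the participant belongs to", and that apart from that person nobody is informed: "only the researcher who will do the irradiations will know". Section 2.8 (Procedure for data collection, blinding, and photobiomodulation) gives assignment to someone else: "An examiner will enroll and assign participants to interventions, performing anthropometric assessments, measurement of hemodynamic variables, and blood collection". It has a different researcher carry out the irradiation.

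**The concern.** A permuted block balances the groups only when it is complete. With four groups and blocks of 8, totals of 40 (10 per group) or 48 (12 per group) end on a complete block, but 44 does not. The group size of 11 is printed as a fixed design figure in two places, yet the only block size given produces it by chance. The article states no rule for the incomplete block.

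What is at stake is agreement between the stated design and the list, more than precision. A reader of the final report who finds 12, 11, 11 and 10 will ask whether the list was followed, and the plan as written gives no answer.

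**Working it through.** **Inputs.** Block size 8 (section 2.6). Total 44, four groups, 11 each (section 2.3 and the group descriptions under Figure 1). Assumption: two places per group in each block of 8, as equal groups imply; the ratio within a block is not stated.

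**The plan's own figure.** 4 × 11 = 44, so total and group size agree with each other. The power calculation behind 44 cannot be reproduced, since its means and standard deviations come from a cited article and are not given. Nothing below depends on it.

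**Complete blocks.** 44 = 5 × 8 + 4. Five complete blocks give 5 × 2 = 10 per group. Participants 41 to 44 fill the first four places of a sixth block.

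**The half block.** There are C(8,4) = 70 equally likely sets of four places out of eight:

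| Split of the last four | Number of sets | Final group sizes | Share of lists |
|---|---|---|---|
| 1/1/1/1 | 2⁴ = 16 | 11/11/11/11 | 22.9% |
| 2/1/1/0 | 4 × 3 × 2 × 2 = 48 | 12/11/11/10 | 68.6% |
| 2/2/0/0 | C(4,2) = 6 | 12/12/10/10 | 8.6% |

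Check: 16 + 48 + 6 = 70. The stated sizes fail to appear in 54/70 = 77.1% of lists. No group can fall below 10 or exceed 12.

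**Replacement.** A replacement inherits the allocation of the patient who left, so the counts set by the list do not change.

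**Cost in precision.** The variance of a difference between two groups is proportional to 1/n₁ + 1/n₂. For 11 v 11 this is 2/11 = 0.1818; for 12 v 10 it is 0.1833. The ratio is 0.992, a loss of 0.8%. Averaged over all six pairs, the variance is proportional to the sum of 1/n over the four groups:

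- 11/11/11/11: 4/11 = 0.3636.
- 12/11/11/10: 1/12 + 2/11 + 1/10 = 0.3652, a loss of 0.4%.
- 12/12/10/10: 2/12 + 2/10 = 0.3667, a loss of 0.8%.

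A single pair can do worse. 11 v 10 keeps 0.1818/0.1909 = 95.2% of the efficiency, and 10 v 10 keeps 0.1818/0.2000 = 90.9%. A 10 v 10 result for one named laser-placebo pair needs both of the other groups to take two places, which is 1 set in 70 (1.4%).

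As an illustration only, take a two-mean comparison (normal approximation, two-sided 5%) set to 95% power at 11 v 11. Power is 94.8% at 12 v 10 and 93.0% at 10 v 10.

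**Predictability.** Someone who knows the block size and every earlier allocation, and always guesses the group with most places left, is right for 3.76 of 8 on average (2 by chance), and 1.14 allocations per block are certain. With fixed, known blocks of 4 it is worse: 2.08 of 4 right (1 by chance), and 1 in every 4 certain.

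**A list that fits.** Four blocks of 8 and three of 4: 4 × 8 + 3 × 4 = 44, and 4 × 2 + 3 × 1 = 11 per group.

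**The case against.** The strongest reply is that nothing harmful follows. If the list is simply followed to number 44, the groups are 10 to 12, the randomisation is intact and the loss of power is negligible. That stands, and it limits how much weight the point can carry.

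A second reply is that an article condenses the full protocol, and handling of a last partial block is a detail of list generation that may be settled there. That also stands as far as silence goes. But the point does not rest on silence: it compares two figures that the article itself prints. The assumption of two places per group in each block is fair to challenge and is stated as an assumption.

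Three stronger readings are tempting and not supported:

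- *Blocks of 8 make 11 per group impossible.* They do not; 23% of lists give it.
- *Staff would have to skip or override entries to reach 11.* The document neither says nor implies this. It is a guess about conduct.
- *The fixed block size makes allocation predictable to the person who enrols.* That requires knowledge of earlier allocations, which section 2.6 limits to the researcher who irradiates. Section 2.8 is in tension with this, because the examiner who enrols is also said to assign participants and measures the hemodynamic variables. The article does not settle who sees the list. If the person who enrols could read it, the problem would be concealment, and block size would hardly matter.

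**Conclusion.** The point holds in a limited form. The stated 11 per group is not a property of the stated randomisation. With two places per group in each block and the list followed to participant 44, equal groups arise in 23% of lists and sizes from 10 to 12 in the other 77%. The 12 v 10 comparison, and the average over all pairs, lose under 1% in efficiency; only an individual pair such as 10 v 10 loses more, and that is rare for a named laser-placebo pair. No inference in the trial turns on it.

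This is a minor inconsistency worth correcting because correction is nearly free. It is not evidence that the randomisation is broken or that allocations can be foreseen. Predictability remains a secondary point, conditional on the person who enrols knowing earlier allocations.

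**What to change.** Before first enrolment, generate the list from block sizes that are multiples of 4 and sum to 44, for example four blocks of 8 and three of 4 in random order. This gives exactly 11 per group. Keep the block sizes and the list from the person who enrols. This matters because blocks of 4 are the more predictable ones when their size is known, so any gain in unpredictability depends on sizes that are both varied and undisclosed.

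If the existing list is kept, restate the group sizes in sections 2.3 and 2.6 as 10 to 12 and say that the list is followed as it stands to participant 44.

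In either case, reconcile sections 2.6 and 2.8 on who assigns participants and who sees the list.

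The cost is one regenerated list and a few changed sentences. Sample size, visits and analysis are unaffected.

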**Figure 1 F1:**
[figure not shown]
Flowchart describing study design, sample composition, and experimental protocol.

Research will be carried out to evaluate the effects of photobiomodulation using 2 ILIB protocols established by the manufacturer of the laser equipment: 60 minutes daily exposure time (Laser 60) and 30 minutes daily exposure time (Laser 30), with respective placebo groups (Placebo 60 and Placebo 30):

Laser 60 (N = 11): will be submitted to the conventional drug treatment previously instituted and ILIB sessions for 60 minutes daily for 5 days, to be repeated after 20 days and, after completing 3 cycles, the patients will be reevaluated 1 month after the end of the proposed therapy.Placebo 60 (N = 11): will be submitted to the conventional drug treatment previously instituted and placebo sessions of ILIB for 60 minutes daily for 5 days, to be repeated after 20 days and, after completing 3 cycles, the patients will be reevaluated 1 month after the end of the proposed therapy. The placebo will be performed by placing a beam obturator at the laser output, so that all noise from the equipment will remain the same as that of the Laser 60 group, but no radiation will be delivered to the target.Laser 30 (N = 11): will be submitted to the conventional drug treatment previously instituted and ILIB sessions for 30 minutes daily, for 10 days, being repeated after 20 days and, after completing 3 cycles the patients will be reevaluated 1 month after the end of the proposed therapy.Placebo 30 (N = 11): will be submitted to the conventional drug treatment previously instituted and ILIB sessions for 30 minutes daily, for 10 days, being repeated after 20 days and, after completing 3 cycles, the patients will be reevaluated 1 month after the end of the proposed therapy. The placebo will be performed with the same obturator method mentioned previously.

During the study, strategies will be follow to improve adherence to intervention protocols, as nursing consultations in the form of a home visit, or not—at the discretion of the participant. In addition, patients who have a prescription for drug therapy should not suspend it. All patients, regardless of pharmacological or nonpharmacological use, will receive guidelines for the nonpharmacological treatment of hypertension, focusing on the need to maintain a healthy lifestyle, minimizing risk factors for hypertensive disease. These orientations include directions for healthy eating with decreased levels of sodium, fat, and sugar; regular physical exercise with the supervision of a professional; the need for quality sleep of at least 6 to 8 hours; abandonment or diminution of smoking; and the need for stress-minimizing leisure. Patients taking medication will have guidelines regarding the adequate use of medications, respecting the dose and prescribed schedule, reinforced.

Patients have autonomy for discontinue interventions and in this case, they will be replaced, but the same allocation will be remaining. Any outcome data collected from patients will be disconsidered and the participants will remain in ambulatory care.

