**Table 1 T1:**
[figure not shown]
Dosimetric parameters proposed for the study.

It is considered that this study has minimal risks since, considering the hypothesis of BP reduction due to vasodilatation caused by photobiomodulation, subjects may present BP decrease with possible presence of clinical signs such as lipothymia, vertigo, complaint of malaise by the patient. If this happens, therapy will be stopped immediately and Trendelenburg maneuvers will be performed to increase venous return and BP.

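### Discontinuers are replaced within the vacated allocation and their outcome data disregarded, so the primary BP comparison is of completers plus replacements, not of the groups as randomised

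*Protocol article*

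**What the plan says.** The rule stands in section 2.6 of the protocol article, after the description of the four groups. On participants who stop: "Patients have autonomy for discontinue interventions and in this case, they will be replaced, but the same allocation will be remaining". On their data: "Any outcome data collected from patients will be disconsidered and the participants will remain in ambulatory care". Read in context, the second sentence refers to the people who discontinued.

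Three other places bear on it:

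- **Treatment stops (section 2.8, below Table 1).** Under the hypothesis that the laser lowers BP, the article warns that "subjects may present BP decrease with possible presence of clinical signs such as lipothymia, vertigo, complaint of malaise by the patient", and adds: "If this happens, therapy will be stopped immediately".
- **Who knows the arm (section 2.6).** "Immediately before starting treatment, the researcher will look at the randomized list" to find the participant's group, and apart from that "only the researcher who will do the irradiations will know".
- **Who enrols (section 2.8).** "An examiner will enroll and assign participants to interventions, performing anthropometric assessments, measurement of hemodynamic variables, and blood collection". The list of those kept blind is short: "In this way, the last researcher and the patients will be blind", where the last researcher is the one who analyses the data.

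BP is the primary outcome (section 2.7). Section 2.9 describes the tests only in general terms and does not define an analysis of all randomised participants.

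**The concern.** Randomisation makes the four groups comparable at the moment of allocation. A rule that later removes people, deletes their outcomes and fills the gap with others changes who is compared. If those removed differ from those kept in their BP response, and the removal differs between laser and placebo, the laser-placebo contrast is biased. No later analysis can repair this if the data were disregarded and nothing was measured after the stop.

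The setting makes such a link plausible. The outcome is BP, the expected adverse reaction is a symptomatic fall in BP, and the obturated placebo delivers no radiation. If the laser works as hypothesised, such reactions should be more frequent on active laser.

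A second issue is how replacements enter. A replacement takes a slot whose arm is already known to at least one member of the team. If that knowledge can reach whoever picks the next participant, allocation is not concealed for that person. With 11 per arm, each replacement is 1/11 = 9% of a group.

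**Working it through.** **The plan's own figure.** Section 2.3 gives 4 × 11 = 44 at 5% significance and 95% power, with no dropout allowance stated. It cannot be recomputed, because the mean, SD, effect size, number of measurements and correlation are not given. The point does not depend on it.

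**How often the rule would apply.** Each participant attends 3 × 5 = 15 or 3 × 10 = 30 sessions. For an assumed discontinuation rate d, P(at least one of 44) = 1 − (1 − d)^44, and the expected number of replacements to reach 44 completers is 44d/(1 − d):

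- d = 5%: 0.90 and 2.3
- d = 10%: 0.99 and 4.9

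**Illustration of size.** No input here is in the article; all are assumptions. Change in systolic BP is normal, with mean -3 mmHg on placebo and -11 on laser (true effect -8). Everyone whose change lies below a cut-off c is removed and replaced by someone who completes. The mean of those kept is

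μ + SD·φ(z)/(1 − Φ(z)), with z = (c − μ)/SD.

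For SD = 12 and c = -25:

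- Laser: z = -14/12 = -1.167, φ = 0.2020, Φ = 0.122 (12% removed). Mean kept = -11 + 12 × 0.2020/0.8783 = -8.24.
- Placebo: z = -22/12 = -1.833, φ = 0.0743, Φ = 0.033 (3% removed). Mean kept = -3 + 12 × 0.0743/0.9666 = -2.08.
- Contrast: -8.24 − (-2.08) = -6.16, about -6.2 mmHg. That is (8 − 6.16)/8 = 23% below the true effect.

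The same formula over other assumptions gives these estimated effects (mmHg, truth -8):

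| SD | c = -20 | c = -25 | c = -30 |
|---|---|---|---|
| 10 | -5.7 | -6.7 | -7.4 |
| 12 | -5.2 | -6.2 | -6.9 |
| 15 | -4.7 | -5.5 | -6.2 |

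**When there is no bias.** With no true effect, let a proportion q discontinue in one arm only, through a tendency that has correlation ρ with BP. The bias in SD units is ρ·φ(z_q)/(1 − q), where z_q is the q-quantile of the standard normal. At ρ = 0 this is zero for every q. In 40,000 simulated comparisons of 11 against 11 completers with ρ = 0 and q = 10%, 20% or 30%, the bias was at most 0.002 SD in size and the two-sided type I error was 4.9% to 5.0%.

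**Concealment.** Section 2.6 says that only the irradiating researcher knows the arm. Section 2.8 has an examiner both enrol and assign, and does not list that examiner as blind. On the first statement, the person enrolling need not know which slot is being refilled. On the second, that person may. The two have to be reconciled.

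**The case against.** The strongest defence concerns reach. Section 2.6 covers participants who choose to stop, while section 2.8 covers therapy stopped on clinical signs. The article does not say that the second ends participation or triggers replacement. This stands: the link to BP falls is plausible but not written.

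The illustration can also be attacked, and fairly. Section 2.8 names symptoms and no BP threshold, so removing everyone beyond a hard cut-off is an extreme form of selection. If discontinuation is unrelated to BP, or is equal and equally selective in all arms with no true effect, nothing is biased.

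A reader might infer more than the article supports in three ways:

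- **That hypotensive reactions would vanish from the results.** The sentence disregards outcome data. It does not say that discontinuations, their reasons or adverse events go unreported.
- **That replacements are simply unrandomised and unconcealed.** The vacated slot came from the random sequence, and section 2.6 restricts knowledge of the arm to the irradiating researcher. Only the weaker statement holds: concealment is not assured.
- **That an inert laser would show a false benefit because unresponsive laser patients leave.** Participants are blind and the equipment noise is the same in the placebo groups, so there is no evident mechanism for arms to differ in this way. No weight should rest on it.

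One defence fails. That an analysis plan may exist does not help, because the article itself states the rule, and an analysis plan that followed it could not use data already disregarded.

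**Conclusion.** The point holds as a design defect. Followed as written, the rule yields a comparison of completers plus replacements, and the primary BP contrast loses the protection of randomisation. This rests on two explicit sentences and needs no assumption.

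The amount of bias is a different matter. It requires discontinuation that is related to BP and differs by arm, and its size and direction are unknown. The figure of about -6.2 mmHg for a true -8, and the range of -4.7 to -7.4, show only that the effect need not be trivial under assumed inputs; they predict nothing about this trial. Impaired concealment for replacements is a possibility left open by the conflict between sections 2.6 and 2.8, not an established fact.

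**What to change.** Delete the replacement sentence and the data-discard sentence in section 2.6. In their place, state that:

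- every randomised participant is analysed in the assigned arm, with all outcome data collected kept;
- the scheduled BP measurements are still sought after discontinuation where the participant agrees (continued ambulatory care makes this feasible but is not itself consent to research measurements);
- discontinuations and their reasons are reported by arm;
- any additional participant receives the next number on the concealed list, in addition to and not in place of those who stopped.

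Also reconcile sections 2.6 and 2.8 on who knows the allocation, and state whether a stop under section 2.8 counts as discontinuation for analysis purposes.

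The cost is an amendment of wording, some follow-up readings, some missing outcomes, and slightly lower precision than 44 completers would give. The stated 95% power should then be described as assuming no dropout. If 11 evaluable per arm is to be protected, 11/(1 − d) rounded up gives 12, 13 or 14 per arm (48, 52 or 56 in total) at assumed dropout of 5%, 10% or 20%.
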